#### Patient-centred outcomes

The patient-centred outcomes of this feasibility study relating to multi-dimensional health (and comprising the proposed primary dependent variables of the future clinical trial) are as follows:

Physiological*: Serum Cortisol, Dehydroepiandrosterone (DHEAS), cortisol: DHEAS ratio, C-reactive proteins (CRP), Interleukin 6 (IL-6), Tumour Necrosis Factor alpha (TNFα), Interferon gamma (IFNy).

Functional: Hand grip strength (Southampton protocol [23]), leg strength and power output [24, 25], Short Physical Performance Battery (SPPB) [26], Katz Index of Independence in Activities of Daily Living (Katz ADL) [27], Fried Frailty Phenotype [2].

Psychological/Emotional: Geriatric Depression Scale (GDS) [28], Hospital Anxiety Depression Scale (HADS) [29], Perceived Stress Scale (PSS) [30].

Cognitive: Standardised Mini-Mental State Examination (SMMSE) [31].

Social: Interpersonal Support Evaluation List (ISEL-12) [32].

*All blood samples will be obtained through the process of phlebotomy (venepuncture). Serum will be analysed for the physiological patient-centred outcomes relating to cortisol and DHEAS (assessed by commercial ELISA kit). C-reactive protein and inflammatory cytokines (IL-6, TNFα, IFNy) will be assayed using a multiplex commercial kit (R&D Systems).

#### Identification, consent and recruitment

##### Identification

To identify potential participants, residents will initially be screened by their care team for the following criteria: aged ≥ 65, no of severe sensory impairments that would profoundly impact upon their ability to participate, able to speak and read the English language, not currently taking part in any other clinical trial which could potentially affect the results of this current study, and with a life expectancy which is greater than the length of the study. Potential participants will first be approached by a member of their regular care team at the care home with an information sheet related to the study and asked if they would either be interested in participating in the study or if they would like to receive more information. The information sheets will contain all of the most pertinent information relating to the study and in particular what it would require from potential participants. Potential participants will be given approximately 1 week, after receipt of the information sheet, to consider whether or not they would like to participate in the study. If potential participants express their interest in the study, a member of the research team will meet with them to provide them with more information on the study, and to address any queries which they may have (Additional file 1).

##### Consent

At this stage, potential participants will also be provided with an informed consent form and asked if they would be interested in participating. If it is deemed that a potential participant lacks the capacity to consent, a personal consultee will be sought. If a personal consultee cannot be found, then a nominated consultee will be sought. All efforts possible will be made in this regard to include participants who lack the capacity to consent within the study, as intrinsically within the research team from a personal and professional perspective we would consider it unethical to exclude potential participants from participating in a study, which can potentially benefit them and their overall health status, simply due to the fact that they lack the capacity to consent.

##### Recruitment

Following consent being obtained from the participant themselves, or the obtainment of a declaration from a consultee, all consented potential participants will be screened for the remaining eligibility criteria relating to frailty status.

#### Randomisation and concealment

To restrict the chances of imbalance between the intervention and control groups within this present study (in addition to the proposed future clinical trial) a stratified block randomisation strategy will be employed [34], in order to achieve balance relating to participant baseline characteristics (covariates) for frailty score and age [35]. This randomisation procedure will be carried out through a computer-generated programme [36], by a competent staff member, otherwise unrelated to the study, and the project as a whole. Allocation concealment will be employed where the researcher responsible for recruiting participants and gathering data from the participants will be unaware of the group to which each participant will be allocated initially until initial data collection is complete, avoiding both conscious and subconscious selection bias [37–39].

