In order to ensure this present study is as scientifically valid as possible a number of precautions have been taken to protect the internal and external validity of the study within its methodological design. First, for each participant, all testing procedures (baseline, post-intervention (6 weeks) and follow-up (12 weeks)) will be conducted at approximately the same time of day (± 2 h). This will be controlled in order to protect the findings of the study from changes in the patient-centred outcomes which may be attributable to circadian variation rather than manipulation of the independent variable [19]. The hypothesis of the study will not be divulged to participants prior to or during the conduction of the study in order to control for any potential degree of demand characteristics; a scenario where participants alter their behaviour and/or answers, in order to align with what they believe is potentially the ‘desired’ outcome of the study. All testing sessions related to patient-centred outcomes will take place at least 24 h after the cessation of the previous training session for each participant. This will be implemented in order to ensure acute fatigue does not only become a contributing factor to the results of the study, specifically relating to the patient-centred outcomes, but also the feasibility of such practice during a proposed future clinical trial. All participants will also be asked to refrain from any relatively high-intensity exercise training up to 24 h prior to each testing session. Due to an independent measures research design being employed, a control group will be employed in order to increase the internal validity of the study, i.e. increases the likelihood that any potential changes in the patient-centred outcomes of the intervention group are due to the intervention and not additional external factors. The order in which patient-centred outcomes are tested will be counter-balanced throughout the study at each assessment time point in order to attempt to protect the study from practice effects, especially in the form of order effects, where a participant has been exposed to a specific order of testing before and as such performs better on subsequent testing procedures of the same material. Stratified-block randomisation of participants (based on frailty score and age) will also be implemented in order to reduce any differences between participants within each of the independent variable groups at baseline. This will also allow for protection against additional threats to the internal validity of the study, such as the influence of passing time (unrelated to the intervention) on participants within the study (maturation), and also protects against potential subconscious selection bias amongst the research team relating to group allocation of participants. Finally, in order to increase the external validity of the study, the eligibility criteria of this present study will be kept as minimalistic as possible (within the limits of safety and reason), in order to allow as inclusive a proportion of this population as possible, and in such producing findings which are applicable to not only those within the study, but to the greater population of frail geriatric older adults within residential care settings.

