#### Sample size

This study aims to recruit a convenience sample of *n* = ~ 48 participants: 24 intervention and 24 regular care control. No formal power calculations were conducted due to the feasibility nature of this study. This estimated sample size is based on optimistic projections following preliminary discussion with care home residents with relation to potential uptake.

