#### Quantitative analysis

Statistical analysis of the patient-centred outcomes will be performed using IBM SPSS (Statistical Package for Social Sciences) software. These analyses will be performed as part of the limited-efficacy testing regarding the potential impact of the intervention on the patient-centred outcomes (proposed primary dependent variables of the future clinical trial). Specifically, for this research, the type of statistical analysis which will be used will be as follows: 2 × 3-way independent measures ANOVA’s (analysis of variance consisting of a two independent variables; the specialised resistance training intervention, and control group, each with three levels: baseline, post-intervention (6 weeks) and follow-up (12 weeks) will be carried out for all patient-centred outcomes. A subsequent post-hoc test will be utilised if a significant main effect or interactions are found. Pearson product correlations will also be utilised between various socio-demographic variables (such as age and sex) and the patient-centred outcomes of this study to assess possible relationships between differences in these socio-demographic factors and changes in the patient-centred outcomes of the study.

Central tendency and variability measurements consisting of the measurement of parameters such as the mean, median and mode, and standard deviation and range of scores respectively, will also be utilised during the analysis of data for illustrative purpose. Significance levels will be set at 0.05 (*p* ≤ 0.05), and effect sizes will be reported for all analyses. Additionally, in order to establish if the assumptions of parametric statistics have been met in relation to the assumption that there is a normal distribution of data, the data will be analysed for skewness and kurtosis. As the quantitative component of this study has not been powered given the feasibility nature of the study, the examination of the efficacy of the intervention to impact these variables is limited and interpretation treated with caution pending the results from the future powered clinical trial. All results will be reported with 95% confidence intervals.

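### The stated ANOVA omits frailty score and age, the two factors used to stratify randomisation, so between-arm standard errors are somewhat too large if those factors are prognostic (minor)

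*Protocol article*

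**What the plan says.** Two places in the protocol article fix the randomisation. Under Design overview: "Stratified-block randomisation of participants (based on frailty score and age) will also be implemented". Its stated purpose there is that it "will also be implemented in order to reduce any differences between participants within each of the independent variable groups at baseline". The section Randomisation and concealment repeats this, naming the aim as "in order to achieve balance relating to participant baseline characteristics (covariates) for frailty score and age", and says that the same strategy is meant for the future trial.

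Quantitative analysis then fixes the model for all patient-centred outcomes: a 2 × 3 ANOVA, described as independent measures, whose factors are "the specialised resistance training intervention, and control group, each with three levels: baseline, post-intervention (6 weeks) and follow-up (12 weeks"). No covariate or stratum term is named. Age returns only in a separate analysis: "Pearson product correlations will also be utilised between various socio-demographic variables (such as age and sex) and the patient-centred outcomes". Frailty appears only as an outcome, because the Fried phenotype is on the list of patient-centred outcomes.

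On size and testing: "24 intervention and 24 regular care control", "Significance levels will be set at 0.05", and "No formal power calculations were conducted due to the feasibility nature of this study".

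**The concern.** Stratifying on a prognostic factor removes its between-stratum variation from the difference between arms. A model without that factor still counts the variation as error. The estimate is then more precise than its reported standard error says, the confidence interval is too wide and the test runs below its nominal level. Correlating age with the outcomes in a separate analysis does not correct this, because it leaves the group effect unadjusted.

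The article promises 95% confidence intervals for all results and makes post-hoc tests depend on a significant main effect or interaction. A standard error that does not match the design therefore reaches the reported results. The article also carries the randomisation scheme into the future trial, where the same mismatch could be repeated.

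**Working it through.** There is no power or precision figure to reproduce, because the sample is a convenience sample.

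**Inputs from the article:** 24 per arm; alpha 0.05 (taken as two-sided); three time points; stratification on frailty score and age.

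**Assumptions, not in the article:** R², the share of outcome variance explained by the strata, 0.1 to 0.4; within-person correlation ρ of 0.5 or 0.7; strata that shift the outcome equally at every time point; outcome SD of 1.

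**1. Unadjusted comparison at one time point.** Reported SE = √(2/24) = 0.289. True SE after stratified randomisation ≈ 0.289 × √(1−R²). The ratio is 1/√(1−R²), and actual alpha = 2 × [1 − Φ(1.96/√(1−R²))].

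| R² | Reported SE / true SE | Actual alpha |
|---|---|---|
| 0.1 | 1.054 | 0.039 |
| 0.2 | 1.118 | 0.028 |
| 0.3 | 1.195 | 0.019 |
| 0.4 | 1.291 | 0.011 |

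A simulation (6,000 trials per scenario, four strata of 12 split 6/6) agrees. At R² = 0.2 the estimate varies with SE about 0.26, against a reported 0.29; adding the strata brings the reported SE to 0.26. Under simple randomisation the true SE is about 0.29. The estimate has therefore gained from stratification, and only its stated uncertainty fails to show it.

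**2. Group main effect of a correct mixed ANOVA.** This compares person means over three time points, whose variance is ρ + (1−ρ)/3. That is 0.667 at ρ = 0.5 and 0.8 at ρ = 0.7. The strata explain a larger share of it: at R² = 0.1, 0.1/0.667 = 0.15 or 0.1/0.8 = 0.125. The SE excess is then 1/√0.85 = 1.085 or 1/√0.875 = 1.069, slightly more than in step 1. Simulated alpha is 0.033–0.036, 0.017–0.024 and 0.009–0.011 at R² 0.1, 0.2 and 0.3. With strata added it returns to about 0.05.

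**3. Group-by-time interaction of a mixed ANOVA.** A stratum effect that is constant over time cancels in a change from baseline. The SE of the difference in change is √(2(1−ρ) × 2/24) = 0.289 (ρ = 0.5) or 0.224 (ρ = 0.7), whatever R² is. The mixed ANOVA reports 0.29 and 0.22, and simulated alpha is 0.047–0.054. There is nothing to correct here unless the strata predict change.

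**4. The ANOVA as literally worded.** If the three measurements per person are treated as independent, the SE for the difference in change is √(2 × 2/24) = 0.41, and the simulated interaction alpha is 0.000–0.004, even at R² = 0. The group main effect has alpha 0.06–0.17, so its SE is too small. Both come from ignoring the repeated measurements, not from omitting the strata.

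**5. Once baseline is a covariate.** Residual variance without strata is 1−ρ². With strata it is (1−R²)(1−r²), where r = (ρ−R²)/(1−R²). The SE ratio is the square root of their quotient, ignoring the few degrees of freedom spent.

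| R² | ρ = 0.7 | ρ = 0.5 |
|---|---|---|
| 0.1 | √(0.510/0.500) = 1.01 | √(0.750/0.722) = 1.02 |
| 0.2 | √(0.510/0.4875) = 1.02 | √(0.750/0.6875) = 1.04 |
| 0.3 | √(0.510/0.471) = 1.04 | √(0.750/0.643) = 1.08 |
| 0.4 | √(0.510/0.450) = 1.06 | √(0.750/0.583) = 1.13 |

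**The case against.** The strongest reply is that the article's model has baseline as one of its time levels, so the effect of training on change is carried by the interaction, which step 3 shows to be unharmed. That stands, and it confines the point to between-arm comparisons at a time point and to the group main effect.

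A second reply is that R² is assumed and may be small. That also stands. Eligibility requires the Fried frail category, which the Background defines as three or more of five criteria; if the stratifying score is that count, it can only be 3, 4 or 5. Some outcomes, such as grip strength, overlap with the Fried criteria, but their own baseline values would absorb much of that.

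A third reply is that covariate terms are often left to an analysis plan, which is not shown here. This carries less weight, because the article goes beyond silence: it names the model for all patient-centred outcomes, and the named model lacks the design factors. A plan that adds them would settle the point.

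A reader might also infer three stronger things:

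- **That stratification is wasted.** It is not. Balance belongs to the allocation and protects the point estimate under any model, and balance is the only purpose the article gives for stratifying.
- **That every standard error is too large.** Steps 3 and 4 contradict this; under the literal wording the main effect errs the other way.
- **That the lost precision distorts the sample size of the future trial.** The article does not say that these estimates will be used for that purpose.

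**Conclusion.** The point holds in a limited form. The stated model does not match the stratified design. If age and frailty are prognostic, unadjusted between-arm comparisons at 6 or 12 weeks carry standard errors about 5%, 12% and 20% too large at R² of 0.1, 0.2 and 0.3. The group main effect of a proper mixed ANOVA is affected slightly more. These sizes depend on the assumed R², for which the low end is plausible. The error is conservative, and it does not reach the interaction of a mixed ANOVA if the strata act on level only.

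Severity is minor: efficacy is a secondary aim, the study is unpowered, and the article already asks for cautious interpretation. Treating repeated measurements as independent is a separate and larger fault of the same section. Correcting that fault alone would leave this mismatch in the group main effect.

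**What to change.** Replace the 2 × 3 ANOVA by a baseline-adjusted model of the 6- and 12-week values: an ANCOVA at each time point, or one repeated-measures model for both. Enter the baseline value of the outcome as a covariate and remove it as a response level, since it cannot properly serve as both. Add age and baseline frailty score as fixed terms for every outcome. Where the Fried phenotype is itself the outcome, its baseline value serves as the frailty term.

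This changes the model wording, so it is more than an added clause. It costs two or three degrees of freedom out of about 48 participants. No new data are needed: age is an eligibility item and frailty is assessed at screening.

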Acceptability	• Will the proposed population be interested in participating in the study? • What will the uptake be? • Will the programme be judged as suitable by the delivers of the programme in addition to the programme participants? • What are participant’s opinions on hypothetically being randomised into a control group during a proposed future clinical trial?* *Participants within the feasibility study will not be recruited as participants within the proposed future clinical trial in order to protect the scientific validity of a future clinical trial, as the participants within the feasibility study will already have undergone the interventions. Additionally, the intervention may be altered after being informed by this feasibility study as well as utilising Patient and Public Involvement (PPI)).	• Participant uptake analysis (all participants approached and eligible for the study/all of those successfully recruited to the study) • Semi-structured interviews with participants • Focus groups with intervention implementers and study support staff.
Demand	• Will the proposed population of care home residents participate in the study? • What will adherence rates be? • Are the staff in the home open to the idea of having an exercise intervention potentially in the home long term if it proves effective?	• Analysis of uptake rates • Exercise intervention adherence rates • Focus groups with study support staff/care home staff.
Implementation	• What are the possible logistical issues with the setting which will need to be addressed or accounted for prior to the clinical trial? • Can the interventions be successfully carried out within this setting? • Can a single or double bind be successfully implemented within the setting?	• Semi-structured interviews with study participants. • More in-depth with focus groups with intervention implementers and study support staff.

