In the qualitative data analysis, clarification of all possible researcher biases will be made known. For example, it will be articulated that the researcher is an advocate of physical activity as a means to promote health, prescribing to the theoretical and practical concept of exercise as medicine, and hence there may be some form of unconscious subjective bias in this context. However, it should also be noted that the researcher within this study is also an advocate of science to an equal or even greater extent, and as such any such bias in subjective analysis would potentially be counteracted in this sense.

Interviews—“a conversation with a purpose” [21] will be the primary method of data gathering utilised within this feasibility study, as it enables large amounts of information to be gathered relatively quickly. Specifically, this study will employ semi-structured interviews, with open questions in a conversational format. There will be a number of pre-determined themes, topics and questions to be discussed, specifically relating to the eight areas of focus of the feasibility outcomes of this study. All interviews will be audio-recorded in order to facilitate future transcription. This will also be the case with focus groups with study support staff and intervention implementers. The qualitative element of this study will also explore opportunities for Patient and Public Involvement (PPI) in the research design of the proposed future clinical trial.

As this study will utilise a mixed-methods research approach, employing both qualitative (feasibility outcomes) and quantitative (patient-centred outcomes) research methods, this will provide researchers with the opportunity of not only gathering the individual data needed from each method of data collection, but will also facilitate the potential for elaboration and expansion of these findings through complementary analysis of each approach. The qualitative aspect of this feasibility study, aimed at assessing the feasibility outcomes, will predominantly take a phenomenological approach to understand the experiences of individuals involved in the study [22].

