#### Data collection

Data within this feasibility study will predominantly be collected at three main time points: baseline, post-intervention, and follow-up (Table 2).

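### The data-gathering researcher's masking is set to end after baseline and no masked assessor is named for the 6- and 12-week tests, so effort-dependent outcomes are open to detection bias and the blinding question rests on opinion.

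*Protocol article*

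**What the plan says.** Randomisation and concealment describes a single role, "the researcher responsible for recruiting participants and gathering data from the participants", and says that this person "will be unaware of the group to which each participant will be allocated initially until initial data collection is complete". The purpose given is "avoiding both conscious and subconscious selection bias". Assessor bias in later measurements is not mentioned.

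Data collection gives three time points: "baseline, post-intervention, and follow-up". The sections on post-intervention assessment and follow-up testing fix time windows and do not say who assesses. The Intervention section adds that machine-use records are open to the researcher at any time.

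Table 1, under Implementation, asks: "Can a single or double bind be successfully implemented within the setting" (the last noun is evidently meant as blind). The methods listed are semi-structured interviews with participants and "More in-depth with focus groups with intervention implementers and study support staff".

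The Feasibility outcomes section discloses, for the qualitative analysis, that "the researcher is an advocate of physical activity as a means to promote health".

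**The concern.** Concealment up to the end of baseline protects against selection bias, and for that purpose the end point is right. It does nothing for outcome measurement. Two of the three time points, and every post-baseline comparison between arms, fall after it. Several outcomes depend on how hard the participant is encouraged or how the tester scores: grip strength, leg strength and power, SPPB, SMMSE. The comparator is regular care, so a tester who knows the arm also knows who has trained. A shift in favour of the exercise arm would enter the limited-efficacy results. Table 1 uses those results to choose testing time points for the future trial, and the Discussion attaches implications to a positive result.

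The study also loses a chance to learn. It asks whether a blind can be implemented but does not run one after baseline, so nothing is observed about whether a blind holds in this home.

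**Working it through.** **Text check**

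1. Masked role: the researcher who recruits and gathers data. Masking ends when initial data collection is complete (Randomisation and concealment).
2. Assessments after that point: post-intervention and follow-up, 2 of 3 (Data collection).
3. Assessor named for those two: none (Post-intervention assessment; Follow-up testing).
4. Safeguards listed in Design overview: same time of day, 24 h since training, counterbalanced test order, hypothesis withheld from participants. Assessor masking after baseline is not among them.
5. Blinding question: assigned to interviews and focus groups (Table 1). These can report whether a blind looks workable; they cannot show that one was kept.

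**Exposure by outcome (Patient-centred outcomes)**

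- Exposed to the assessor: grip strength, leg strength and power, SPPB, SMMSE and other assessor-administered measures.
- Little exposed: cortisol, DHEAS and their ratio, CRP, IL-6, TNFα, IFNγ (laboratory assays).
- Partly outside the assessor's influence: GDS, HADS, PSS and ISEL-12, so far as they rest on participants' own answers. Reporting bias from participants who know their arm would remain even with a masked assessor.

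**Illustrative size**

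The article gives no SD, effect size or power, so there is no figure of its own to reproduce. From the article: 24 per arm (Sample size) and significance level 0.05 (Quantitative analysis), taken as two-sided. Assumed: true effect zero, outcome SD = 1, assessor shift b = 0.1, 0.2 or 0.3 SD, and a baseline-to-later correlation of 0.7 for the change score. The planned ANOVAs have no baseline covariate, so two simple comparisons at one time point are used:

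- Unadjusted: SE = √(2/24) = 0.289
- Change score: SE = √[(2/24) × 2 × (1 − 0.7)] = √0.05 = 0.224

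False-positive rate = P(|Z + b/SE| > 1.96), normal approximation:

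| b (SD) | Unadjusted: b/SE | Rate | Change score: b/SE | Rate |
|---|---|---|---|---|
| 0 | 0 | 5.0% | 0 | 5.0% |
| 0.1 | 0.346 | 6.4% | 0.447 | 7.3% |
| 0.2 | 0.693 | 10.7% | 0.894 | 14.5% |
| 0.3 | 1.039 | 18.0% | 1.342 | 26.9% |

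With a correlation of 0.5 the change-score SE is also 0.289 and the two columns coincide. The exact t-test for the unadjusted comparison (46 degrees of freedom) gives 6.3%, 10.4% and 17.5%. With an assumed 19 completers per arm it gives 6.0%, 9.2% and 14.7%. Fewer participants lower the false-positive rate, but the bias in the estimate stays at b.

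**The case against.** - **The assessor may be someone else.** The sentence is about allocation concealment, and a condensed article may leave assessor assignment to the full protocol. This stands in part: that the same researcher does the later tests is an inference. It is the natural one, since the article speaks of one data-gathering researcher and names no other assessor. If a masked assessor is intended, one sentence settles the matter.
- **A reader might infer that the study cannot answer its blinding question at all.** The article does not support that. Table 1 assigns a method, and interviews and focus groups will give views on workability. What is missing is an observed result.
- **A reader might take the researcher's declared advocacy, and the remark that it is counterbalanced, as the plan's defence of its outcome testing.** That passage concerns the qualitative analysis only. It shows a prior belief and says nothing about the physical or cognitive tests.
- **Efficacy is secondary and already caveated.** This is true and limits the consequence. No section says that the effect estimates will size the next trial. But the caution under Quantitative analysis rests on lack of power, and a larger trial cures imprecision, not assessor bias.
- **Masking may fail in a single home with group sessions.** This is fair. It is a reason to measure unmasking, since that is what the feasibility question asks.

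**Conclusion.** The point holds in a limited form. The article sets the data gatherer's masking to end at baseline and provides no masked assessment afterwards, so the assessor-administered outcomes at 6 and 12 weeks are open to detection bias that the stated caution does not cover. The Table 1 blinding question will be answered by opinion only. For shifts of 0.1 to 0.3 SD the false-positive rate per exposed outcome rises from 5% to somewhere between about 6% and 27%. The shifts and the correlation are assumptions, and 24 per arm is described in the article as an optimistic projection; the figures show how sensitive the results are and do not estimate the actual bias. The conclusion also rests on the inference that the same researcher, or another unmasked one, does the later tests. The primary feasibility aim is otherwise unaffected. The change is worth making because it is cheap.

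**What to change.** 1. In Randomisation and concealment, move the end of masking to completion of the last follow-up assessment for whoever tests the patient-centred outcomes, and state who that is.
2. Leave session delivery to the trainer and implementers, and the allocation list with them and the unrelated staff member who runs the randomisation.
3. Give the assessor no access to the machine database until follow-up testing ends.
4. Hold any participant interview that the assessor conducts until after that participant's last follow-up test, or have another existing team member conduct it. The second researcher is in the plan only to analyse qualitative data, so interviewing would be an added duty for that person.
5. At the 6- and 12-week assessments, record the assessor's guess of arm and any unmasking. This answers the Table 1 question with data.
6. If masking fails, report the affected efficacy estimates as unmasked.

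The sample size stays at about 48 and no extra assessor or test is required. The cost is less flexible staffing and possibly later interviews. Unmasking may be common in this setting, and the guess record would show how common. Bias in self-reported scales from participants who know their arm is not removed by this change.
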